### Study protocol, variables part two (follow-up)

Admitted to hospital ward (yes, no, don’t know).

Received any of following interventions: ICD, PCI/PTCA, CABG (yes, no, planned, don’t know), hypothermia, beta-blocker (yes, no, don’t know).

Discharged alive from hospital: (yes, no, don’t know).

If yes, discharged to: (home, other hospital, other, don’t know).

If yes, discharge date (xx-xx-xx, don’t know).

If yes, CPC score at discharge (1–5, don’t know).

Death within 30 days of CA: (yes, no, don’t know).

If yes, date of death (xx-xx-xx, don’t know).

Follow-up completed ( ).

#### CPC (Cerebral Performance Categories) score

•CPC 1 (no disability).

•CPC 2 (slight disability).

•CPC 3 (moderate disability).

•CPC 4 (comatose/vegetative state).

•CPC 5 (death).

### Data collection

The main variables will be collected by EMS staff from ambulance records. Ambulance delay will be collected from dispatch records. Survival data and CPC score will be collected from hospital records. CPC score will be assessed by health care personal at hospital, blinded to the study protocol. To minimise missing data, the study protocol (database) will be compared with dispatch records. Personal data collected and stored for the purposes of this study will be treated pursuant to the applicable paragraphs of the Organic Law of Personal Data Protection 15/1999, dated 13 December.

### Clinical report form (CRF)

1. Staff member 1: confirm CA and start immediate chest compression.

2. Staff member 2: open defibrillator bag (with envelope and PLR reminder glued to the defibrillator).

3. Staff member 2: open envelope and randomize to PLR or flat position.

4. Staff member 2: if PLR, use the folding stool in the rescue bag.

5. Staff member 2: ventilate the patient once and attach defibrillation pads.

6. Continue resuscitation according to guidelines.

7. If PLR: keep the position as long as the patient is receiving chest compressions.

PLR has to be performed during the first minutes. If PLR is performed later than five minutes after the start of CPR: mark “forgot” on the data sheet.

Web registration: fill in the study protocol for all patients aged ≥18 years receiving out-of-hospital CPR. If not included in the study: just fill in the first part.

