### Method and design

A prospective, randomized, controlled trial in which all patients (≥18 years) receiving out-of hospital CPR are randomized by envelope to be treated with either PLR or in a flat position. The ambulance crew use a special folding stool, which allows the legs to be elevated about 20 degrees.

The PLR manoeuvre needs to be performed immediately (within five minutes) after the arrival of the first ambulance. Leg elevation has to be maintained while the patient receives chest compressions during CPR and has to be stopped when the patient has an ROSC or when a medical decision is made to interrupt these maneuvers. PLR is to be performed at an angle of between 20 and 45 degrees (approximately 35 to 40 cm). An instruction video is produced for training prior to the study; the aim of using a specially designed folding stool is to standardise the intervention as much as possible.

In the start-up phase between June 2013 and April 2014, the study has only been conducted in the City of Tarragona and the surrounding areas. In all, 13 mobile units (12 BLS and one ALS unit) will attend (attended) in the start-up phase. Since April 2014, a further 56 units, the whole province, have been participating in the study. The study will continue for three years.

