### Study protocol, variables, part one (EMS)

Ambulance journal number, district, ambulance unit, date.

Randomization: yes (randomization number, PLR Y/N), no (forgot, <18 years, rigor mortis).

Time: of CA, call to dispatch centre, alert ambulance, start ambulance, arrival address, arrival at patient’s side, start CPR, first defibrillation, ROSC time, start transport to hospital, arrival hospital.

Patient data: age, gender, date of birth.

Data on the OHCA incident:

a) Place of occurrence (home, street…)

b) Witnessed: yes (bystander, ambulance staff), no

c) CPR before ambulance arrival: yes (layperson etc.…), no.

d) If CPR before ambulance: defibrillation Y/N (number), ventilation Y/N, chest compression Y/N, telephone CPR Y/N.

e) Status at ambulance arrival: unconscious Y/N, breathing (normal, agonal, no), pulse Y/N.

f) Initial rhythm:

g) Semi-automatic defibrillator: (defibrillation, no defibrillation).

h) If information about rhythm: (VF, VT, PEA, asystole).

i) Reason for CA: (cardiac cause, intoxication, drowning, suicide, accident, pulmonary disease, infant death, asphyxia, other reason).

j) Treatment: (chest compression, mechanical compression, ventilation, intubation, defibrillation (number), epinephrine, atropine, amiodarone, hypothermia.

k) Result: return of spontaneous circulation (ROSC), to hospital Y/N (if yes, which hospital).

l) If arrival hospital: pulse-giving rhythm Y/N, conscious Y/N.

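### Late leg raise is coded 'forgot', a reason for not being randomized, so the form can misfile randomized patients in the PLR arm only

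*Protocol article*

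**What the plan says.** All references are to the protocol article.

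- **Clinical report form (CRF), step 3:** the second crew member is to "open envelope and randomize to PLR or flat position".
- **Same section, step 4:** "if PLR, use the folding stool in the rescue bag". Randomization therefore comes before the manoeuvre.
- **Same section, below the steps:** "If PLR is performed later than five minutes after the start of CPR: mark “forgot” on the data sheet".
- **Study protocol, variables, part one (EMS):** the randomization item has two branches. The yes branch asks for the randomization number and PLR Y/N. The other branch reads "no (forgot, <18 years, rigor mortis" and asks for no number. 'Forgot' appears nowhere else on the form.
- **Clinical report form, web registration:** "If not included in the study: just fill in the first part".
- **Study protocol, variables part two (follow-up):** this part holds "Death within 30 days of CA", from which the primary end-point (survival to one month) is derived. Under Data registration, part two applies to patients admitted alive.

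**The concern.** A patient whose envelope has been opened is randomized, whatever the crew does next. The late-PLR rule gives such a patient a code that the form treats as a reason for not having been randomized, beside being under age and rigor mortis. The rule depends on PLR being performed, so it can apply to one arm only.

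If these patients are then handled as not included, the PLR arm loses patients after allocation on the basis of something that happened during the resuscitation, and the flat arm loses none. The comparability given by randomization would no longer hold. If late-PLR patients survive less often than average, the remaining PLR arm looks better than it is. If they survive more often, a real benefit is partly hidden.

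**Working it through.** **1. Follow two patients with the same six-minute delay.**

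| | PLR card | Flat card |
|---|---|---|
| Envelope opened | yes | yes |
| Manoeuvre that can be late | yes | none |
| Code under the late rule | 'forgot' | not applicable |
| Branch of the randomization item | no | yes |
| Randomization number asked for | no | yes |
| Part two if admitted alive | may be skipped | completed |

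The asymmetry remains even if the delay came from opening the envelope late: the PLR card leads to 'forgot' and the flat card does not.

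**2. The plan's own figures.** Inputs from the sample size section: 7% against 10% survival, 80% power, two-sided 5%, 1,490 per arm. The test for dichotomous variables is Fisher's exact test (Statistical analysis). The pooled normal formula gives 1,356 per arm, the continuity-corrected formula 1,422, and exact enumeration of Fisher's test about 1,415. The stated 1,490 is not reproduced, but it is on the safe side: exact Fisher power at 1,490 is 82%. The point does not depend on this gap.

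**3. Illustration of one-sided removal with no treatment effect.** True survival is 7% in both arms, with 1,490 randomized to each. A share g of the PLR arm is removed, with survival s. Both g and s are assumptions, because the article gives neither. Survival in the PLR patients who remain is

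(0.07 − g·s) / (1 − g)

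For example, g = 10% and s = 0 gives 0.07/0.90 = 7.78% in 1,341 patients, compared with 7.00% in 1,490 flat patients. Each cell shows remaining PLR survival, then the exact two-sided Fisher error.

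| g (patients removed; left) | s = 0% | s = 3.5% | s = 7% |
|---|---|---|---|
| 2% (30; 1,460) | 7.14%; 4.9% | 7.07%; 4.7% | 7.00%; 4.6% |
| 5% (74; 1,416) | 7.37%; 6.2% | 7.18%; 5.0% | 7.00%; 4.6% |
| 10% (149; 1,341) | 7.78%; 11.7% | 7.39%; 6.4% | 7.00%; 4.6% |

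With nobody removed the error is 4.2%. The step from 4.2% to 4.6% in the last column is not bias. It comes from the discreteness of Fisher's test once the arm sizes differ. Only the excess over about 4.6% reflects distortion.

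**The case against.** Several points on the other side have weight.

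- **Exclusion is inferred.** The late rule says only what to write on the data sheet. It does not tell the crew to answer no to randomization, to discard the number, or to treat the patient as not included. The conclusion joins three lines of a condensed form listing. The yes branch, with its PLR Y/N field, might be read as able to hold a PLR patient who was not treated as allocated. This stands as a limit. It does not remove the defect, because 'forgot' has no other place on the form.
- **The analysis set belongs to the full protocol or SAP.** True, and its absence here is not criticised. The fault is in a coding rule that the article does state. An intention-to-treat plan cannot by itself repair records filed as not randomized.
- **Little outcome data is at risk.** Patients who die before admission have their result in part one. Only late-PLR patients admitted alive could lose part two. That is correct, but every one-month survivor is in that group.
- **The data may be recoverable.** Envelopes are numbered, the allocation list is kept, and survival comes from hospital records. This may work, but the form asks for no number under the no branch, and no one is told to make the link.
- **The sizes are assumed.** Also true. At 3.5% survival among those removed the effect is small, and at 7% there is none.

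Two stronger readings are tempting. A reader might infer that the trial plans to drop late-PLR patients from the analysis. The article nowhere says so. A reader might also infer that the rule favours PLR, since these patients were still receiving compressions after five minutes. Below-average survival is plausible on that ground, but the documents contain nothing on how late-PLR patients fare, so the direction is not established.

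**Conclusion.** The defect is in the stated text. A code that belongs to patients never randomized is prescribed for patients who have been randomized, and it can reach the PLR arm only. What follows from it is conditional: a bias arises only if the coded patients are in fact treated as not included, their records are not recovered, and their survival differs from that of the rest of the arm. The article settles none of these, so the direction and size of any bias are unknown.

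Under the assumptions above, the effect on the error rate ranges from none to a rise to 11.7%. The top figure needs both a 10% late share and no survivors among those removed. This should be corrected, because the correction is cheap and recruitment is already under way. Confidence is medium.

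**What to change.** **Change.**

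- Use 'forgot' only when no envelope was opened.
- Record late or omitted PLR under the yes branch, with the randomization number and an adherence flag.
- Complete part two for every patient with an opened envelope who is admitted alive. Count the others by their part-one result.
- Analyse each patient in the allocated arm.

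**Cost.** One recoded form item, a notice to units already recruiting, and some added follow-up. Keeping late patients also dilutes the effect if late PLR does nothing. With late patients at 7% and the rest of the PLR arm at 10%, PLR survival is (1 − g)·10% + g·7%, which is 9.94%, 9.85% or 9.70% for 2%, 5% or 10% late. Exact Fisher power at 1,490 per arm is then 81%, 78% or 74%, against 82% with none late. This is the price of a comparison that randomization still protects.

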### Education/time plan

#### First semester 2013

Introduction of the study, CRF video and basic training of the ALS and BLS teams in the City of Tarragona and surrounding areas. The study was started in Tarragona and surrounding areas on 1/6/2013.

#### First semester 2014

Introduction of the study, CRF video, web journal and basic training of the remaining ALS and BLS teams in the district of Tarragona. The study started in the remaining part of the district on 1/4/2014.

### Ethical approval

The study has the ethical approval of the Ethical Research Committee in Tarragona (CEIC 15/2013) and Reus (13-04-25/4aclaobs1).

## Discussion

The Swedish pilot study [22] was approved by the ethics committees at Stockholm and Gothenburg Universities in March 2003. However, when we applied for new approval in 2011, the study was rejected due to the lack of informed consent. At the moment, there is a debate in Sweden about the opportunity to perform studies of different treatments on unconscious patients. One important issue in the debate is that clinicians find it difficult, time consuming and unethical to ask next of kin, who are upset, for their informed consent in acute situations.

Before we started the present intervention in Spain, we performed our power analysis according to an estimated survival of 7%. In their reports from Spain, Rosell Ortiz [35] and Alvarez Fernandez [36] stated a survival rate of around 10% and an incidence of 25/100,000 EMS-treated OHCAs. Bystander CPR was reported to be performed in about 15% of all cases. Compared with Sweden, the survival rate was similar (10%), but the incidence of EMS-treated OHCA was twice as high (50/100,000) in Sweden [37]. The reason for this can only be speculated on, but shorter ambulance delay in combination with a higher proportion of bystander CPR in Sweden (68%) might be an explanation. Another possible explanation could be the higher competence level in the Spanish ALS units. Compared with the Swedish nurse-staffed ambulances, the Spanish physician-staffed ALS units might have the opportunity to cease resuscitation more frequently [38].

The Swedish pilot study revealed increased EtCO_2_ during PLR, which we interpret as improved cardiac preload and blood flow to the heart and brain during chest compressions. The benefit was greatest when the rescuer performed manual chest compressions [22]. The previous study of PLR was made at an angle of 20 degrees, but, in the present study, we decided to allow the angle to range from 20 to 45 degrees to make the clinical application more flexible. However, the chief researcher (CR) in Tarragona has equipped all the units with a folding stool made of plastic to enable the legs to be elevated 22 centimetres (about 20 degrees).

### Limitations

The power calculation is based on an estimated survival rate of 7%. If the survival rate is lower, we will need a larger sample than calculated. With regard to the outcome of the treatment during OHCA, it may be that the chance of survival does not increase. In no case, however, is there any risk to the participants.
